## < Clinical Trial Protocol >

|                            |                                                                                                                                                                                    |                                                                                                                                                                                                                                                                                                                                                                                                                                                                                                                                                                                                                                                                                                                                                                              |                                                                                                                                                                                      |
|----------------------------|------------------------------------------------------------------------------------------------------------------------------------------------------------------------------------|------------------------------------------------------------------------------------------------------------------------------------------------------------------------------------------------------------------------------------------------------------------------------------------------------------------------------------------------------------------------------------------------------------------------------------------------------------------------------------------------------------------------------------------------------------------------------------------------------------------------------------------------------------------------------------------------------------------------------------------------------------------------------|--------------------------------------------------------------------------------------------------------------------------------------------------------------------------------------|
| Objectives                 | This clinical trial aims to demonstrate the improvement of memory and cognitive function using transcranial magnetic stimulation applied to the patients with Alzheimer's disease. |                                                                                                                                                                                                                                                                                                                                                                                                                                                                                                                                                                                                                                                                                                                                                                              |                                                                                                                                                                                      |
| Clinical Trial Institution | Samsung Medical Center                                                                                                                                                             |                                                                                                                                                                                                                                                                                                                                                                                                                                                                                                                                                                                                                                                                                                                                                                              |                                                                                                                                                                                      |
| Clinical Trial Sponsor     | [name], Professor, Samsung Medical Center                                                                                                                                     |                                                                                                                                                                                                                                                                                                                                                                                                                                                                                                                                                                                                                                                                                                                                                                              |                                                                                                                                                                                      |
| Clinical trial duration    | 2018.10~2020.10 (24 months)                                                                                                                                                        |                                                                                                                                                                                                                                                                                                                                                                                                                                                                                                                                                                                                                                                                                                                                                                              |                                                                                                                                                                                      |
| Clinical trial design      |  non-randomized allocation
 randomized allocation                                                                    |  single arm design
 parallel desing
 cross-over design                                                                                                                                                                                                                                                                                                                                                                                                                                                                                                                                                                                                                   |  open labeled
 single blinded
 double blinded
 evaluator blinded |
| Subject                    | Inclusion criteria                                                                                                                                                                 | 1) aged between 55 and 90 years
2) diagnosed as either mild cognitive impairment due to AD or mild AD dementia on the basis of National Institute on Aging–Alzheimer’s Association criteria, with amyloid positivity determined by PET or CSF testing
3) Objective memory impairment as indicated by at least 2 standard deviations below the age- and education-adjusted mean in verbal language test (SVLT) or Rey-copy figure test (RCFT) delayed recall tests
4) $\geq 18$ of Mini-Mental State Examination (MMSE) score
5) no history of epilepsy
6) normal in electroencephalography (EEG)
7) no myocardial infarcts or arrhythmia in electrocardiography (ECG)
8) those who are literate
9) those who voluntarily submitted written consents. |                                                                                                                                                                                      |
|                            | Exclusion criteria                                                                                                                                                                 | 1) with other medical or surgical diseases that caused                                                                                                                                                                                                                                                                                                                                                                                                                                                                                                                                                                                                                                                                                                                       |                                                                                                                                                                                      |

|         |                    |                                                                                                                                                                                                                                                                                                                                                                                                                                                                                                                                                                                                                                                                                                                                                                                                                                                                                                                                                                                                                                                                                                                            |                 |
|---------|--------------------|----------------------------------------------------------------------------------------------------------------------------------------------------------------------------------------------------------------------------------------------------------------------------------------------------------------------------------------------------------------------------------------------------------------------------------------------------------------------------------------------------------------------------------------------------------------------------------------------------------------------------------------------------------------------------------------------------------------------------------------------------------------------------------------------------------------------------------------------------------------------------------------------------------------------------------------------------------------------------------------------------------------------------------------------------------------------------------------------------------------------------|-----------------|
|         |                    | 
dementia;
 
2) with severe white matter hyperintensities (WMH) on magnetic resonance image (MRI), which were defined as deep WMH <math>\geq 25</math> mm and periventricular WMH <math>\geq 10</math> mm;
 
3) who could not undergo MRI due to side effects related to contrast agents, or claustrophobia; 4) who have implanted medical devices that are susceptible to electronic disturbance, such as pacemaker, or detachable metallic materials (prosthetics, braces, cochlear implants etc.);
 
5) who have undergone cerebrovascular surgery, such as coiling clipping, and carotid artery stenting;
 
6) who have difficulty breathing when sitting;
 
7) who have lost consciousness for more than one hour due to causes other than general anesthesia;
 
8) who have been hospitalized with a head trauma;
 
9) who cannot read even with glasses due to reduced vision;
 
10) who have difficulty understanding conversations due to hearing impairment even with a hearing aid;
 
11) who have taken ototoxic drugs or have been exposed to loud noises.
 |                 |
|         | Number of subjects | rTMS group                                                                                                                                                                                                                                                                                                                                                                                                                                                                                                                                                                                                                                                                                                                                                                                                                                                                                                                                                                                                                                                                                                                 | 16 participants |
|         |                    | Sham group                                                                                                                                                                                                                                                                                                                                                                                                                                                                                                                                                                                                                                                                                                                                                                                                                                                                                                                                                                                                                                                                                                                 | 16 participants |
| Methods | Target selection   | Using the findings from resting-state functional MRI analysis, a specific area in the left lateral parietal region, characterized by the strongest connectivity with the hippocampus, was pinpointed. This particular area was chosen as the focal point for stimulation and precisely positioned using a medical guide during the rTMS treatment.                                                                                                                                                                                                                                                                                                                                                                                                                                                                                                                                                                                                                                                                                                                                                                         |                 |

|  |                       |                                                                                                                                                                                                                                                                                                                                                                                                                                                                                                                                                                                                                                                                                                                                                                                                                                                                                                                                                                                   |
|--|-----------------------|-----------------------------------------------------------------------------------------------------------------------------------------------------------------------------------------------------------------------------------------------------------------------------------------------------------------------------------------------------------------------------------------------------------------------------------------------------------------------------------------------------------------------------------------------------------------------------------------------------------------------------------------------------------------------------------------------------------------------------------------------------------------------------------------------------------------------------------------------------------------------------------------------------------------------------------------------------------------------------------|
|  | Stimulation procedure | 
Intensity : motor threshold 100%
 
The motor threshold was determined for individual patients by placing a magnetic coil over the motor cortex and adjusting the stimulation intensity to elicit a visible contraction of the patient's hand. The intensity was adjusted to 100 % of the motor in the left parietal area and was treated during the same daily session.
 
Number of pulses : 1600 pulses
 
Each area was stimulated with 40 trains (20 Hz for 2 s at 40 pulses/train), equating to 1600 pulses applied daily. All rTMS applications followed the guidelines for the therapeutic use of rTMS. The sham group was exposed to recorded pulse sounds without magnetic stimulation.
 
Duration:
 
- duration: four weeks
 
The stimulation takes approximately 20 minutes per session, and it is administered five times a week (Monday to Friday) for a total of 20 sessions over the course of four weeks.
 |
|  | Medical device        | 
1. ALTMS
 
 
- manufacturer: (주) REMED
 
- magnetic field intensity: 2.5 T
 
- magnetic field frequency: max 100Hz, min 0.1Hz
 
- stimulation time: user-adjustable in increments of 0.1 seconds
 
- output waveform: Symmetric biphasic pulse
 
- pulse width: 350 <math>\mu</math>s
 
- magnetic field generation transducer: 8-coil type
 
- weight: 60kg
 
- power recruitment: 200~ 240 Vac 50/60 Hz
 
 
2. stimulator positioning guide
 
 
- manufacturer: Anymed corp
 
 
-3D-printed medical guide for accurate positioning of the transducer of the medical electromagnetic generator on the patient's skull to provide precise guidance for treatment location information.
                                                                                                                           |
|  | rTMS group            | rTMS stimulation                                                                                                                                                                                                                                                                                                                                                                                                                                                                                                                                                                                                                                                                                                                                                                                                                                                                                                                                                                  |

|          | Sham group       | Sham coil stimulation |                                                                                                                                                                                                                                                                                                                                                                                                                                                                                                                                                                                                                                                                                                                                                                                                                                                                                                                                                                                                                                                                                                                                                                                                               |
|----------|------------------|-----------------------|---------------------------------------------------------------------------------------------------------------------------------------------------------------------------------------------------------------------------------------------------------------------------------------------------------------------------------------------------------------------------------------------------------------------------------------------------------------------------------------------------------------------------------------------------------------------------------------------------------------------------------------------------------------------------------------------------------------------------------------------------------------------------------------------------------------------------------------------------------------------------------------------------------------------------------------------------------------------------------------------------------------------------------------------------------------------------------------------------------------------------------------------------------------------------------------------------------------|
| outcomes | Outcome measures | Primary outcome       | Change in ADAS-Cog scores before and 8 weeks after stimulation in the rTMS group.                                                                                                                                                                                                                                                                                                                                                                                                                                                                                                                                                                                                                                                                                                                                                                                                                                                                                                                                                                                                                                                                                                                             |
|          |                  | Secondary outcome     | 
<Comparison Before and After rTMS Stimulation>
 
The change in scores at baseline, 4 weeks, and 8 weeks based on neuropsychological assessments (K-MMSE, K-MoCA, CDR-SOB, ADAS-Cog/COWAT, Stroop, TMT, RVP, SWM, PRM) in the rTMS stimulation group. The change in total scores derived from K-GDS short form between baseline, 4 weeks after stimulation, and 8 weeks after stimulation.
 
The change in S-IADL scores between baseline, 4 weeks after stimulation, and 8 weeks after stimulation.
 
Functional network changes in resting fMRI at 4 weeks after stimulation.
 
Change in FA values in DTI analysis at 4 weeks after stimulation.
 
<Comparison between rTMS and Sham Groups>
 
 
- The changes in scores of K-MMSE, K-MoCA, CDR, ADAS-Cog, COWAT, Stroop, TMT/PRM, RVP, and SWM between the rTMS treatment group and the sham group are compared.
 
- The changes in FA values in MRI DTI analysis between the rTMS treatment group and the sham group are compared.
 
- Qualitative comparison of functional network changes in fMRI between the rTMS treatment group and the sham
 
 |

|            |                                                                                      |                                  |        |  |  |  |
|------------|--------------------------------------------------------------------------------------|----------------------------------|--------|--|--|--|
|            |                                                                                      |                                  | group. |  |  |  |
|            | Safety evaluation                                                                    | - vital sign
- adverse effect |        |  |  |  |
| Evaluation | Independent Assessment by Three Clinical Trial Investigators
(Neuropsychologists) |                                  |        |  |  |  |

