## **1. Clinical Trial Title**

The effects of transcranial magnetic stimulation (ALTMS) on cognition in the patients with Alzheimer's disease: A single centered, randomized, evaluator-blinded, exploratory clinical trial

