## 6. Objective and Background

### A. Objectives

This clinical trial aims to demonstrate the improvement of memory and cognitive function using transcranial magnetic stimulation applied to the parietal region in patients with Alzheimer's disease.

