#### ● Alternative Hypotheses:

-There will be a significant difference in cognitive abilities before and after receiving 4 weeks of rTMS stimulation.

-There will be a significant difference in cognitive abilities between the group that received 4 weeks of rTMS stimulation and the group that received sham stimulation.

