## **D. Sample Size Determination**

●Target number of participants: 32 participants (sham group 16 and rTMS group 16)

The rationale for the number of participants is based on previous studies. Koch et al. (2008) conducted a study involving 14 Alzheimer's disease patients to investigate the relationship between transcranial magnetic stimulation and cognitive function. Additionally, Wang et al. (2014) reported results from a study with 16 patients showing improvement in associative memory through transcranial magnetic stimulation.

Based on these previous studies, this current study aims to explore the changes in memory and cognitive function by applying transcranial magnetic stimulation to individuals with Alzheimer's disease. This study is an exploratory investigation led by researchers, with 16 patients in each experimental and control group, totaling 32 patients, to assess the extent of cognitive function changes. This study serves as an exploratory study for setting the sample size and evaluating cognitive function changes for future confirmatory clinical trials. In these trials, the effects of transcranial magnetic stimulation will be examined in a larger population of Alzheimer's disease patients, and achieving this goal will require further research.

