### 13.2. Statistical Analysis of the Efficacy

This study is an exploratory, investigator-driven clinical trial. Initially, instead of applying statistical analysis for clinical efficacy, the focus will be on exploring the differences in the changes of primary and secondary variables before and after the application of rTMS (or Sham coil) in the experimental and sham groups. The aim is to investigate how much difference exists and to describe these findings through exploratory research.

Additionally, for the statistical analysis of clinical efficacy, a linear mixed-effects model will be employed. This model will incorporate the intervention group, time points, and other key covariates as fixed effects. This approach will allow for the assessment of the intervention's impact over time while accounting for individual variations and potential confounding factors.

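### The objective and hypotheses are worded as confirmatory, but the title, 7.D and the opening of 13.2 declare an exploratory trial; the aim should be to estimate the rTMS-sham difference

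*Protocol*

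**What the plan says.** **Confirmatory wording.** The Objectives row of the protocol synopsis says "This clinical trial aims to demonstrate the improvement of memory and cognitive function", and section 6.A uses the same sentence. Section 6.A has it as "This clinical trial aims to demonstrate the improvement of memory and cognitive function using transcranial magnetic stimulation applied to the parietal region". Section 7.A gives paired null and alternative hypotheses, one pair for before versus after rTMS and one for rTMS versus sham. The second alternative begins "There will be a significant difference in cognitive abilities between the group that received 4 weeks of rTMS stimulation" and contrasts that group with sham.

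**Exploratory wording.** Section 1 titles the study "A single centered, randomized, evaluator-blinded, exploratory clinical trial". Section 7.D takes its 32 patients (16 per arm) from the head-counts of two earlier studies, with 14 and 16 patients. It adds "This study serves as an exploratory study for setting the sample size" and leaves confirmation to later, larger trials. The first paragraph of 13.2 says that initially, "instead of applying statistical analysis for clinical efficacy, the focus will be on exploring the differences".

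**Efficacy analysis.** The second paragraph of 13.2 adds a linear mixed-effects model for clinical efficacy, with group, time points and key covariates as fixed effects.

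**Primary outcome.** The synopsis and the primary objective in 6.A make it the ADAS-Cog change to 8 weeks within the rTMS group. They list rTMS versus sham as secondary. Section 9.A labels the primary a single-arm design and names ten test scores at 8 weeks. Section 13.1.A names the ADAS-Cog change and adds a difference in change scores, without saying between what.

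**The concern.** The objective and hypotheses are the yardstick by which the result will be read. Here they ask for proof of improvement, while the rest of the protocol describes a study meant to help size the trial that would supply that proof. Both cannot be the purpose.

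Under the present wording, a non-significant comparison with sham would read as failure although it leaves sizeable effects open. A significant one would read as demonstrated although, at this size, the estimates that reach significance tend to be too large. A significant pre-post change in the rTMS arm would meet the stated primary, yet it could reflect practice, expectation or regression to the mean. The quantity the randomised design is best placed to give, the rTMS-sham difference with its uncertainty, is not the headline aim.

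**Working it through.** **Inputs.** From the protocol: 16 per arm, 1:1 (7.D); primary within the rTMS arm (synopsis, 6.A). The protocol gives no alpha, power, effect size, SD or dropout rate, so its 32 can be neither reproduced nor refuted. Assumptions: two-sided 5% level; effects d in units of the SD of ADAS-Cog change; t-tests, unadjusted unless stated.

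**1. rTMS versus sham, n = 16 per arm.** Power is the probability that a noncentral t on 2n − 2 = 30 df, with noncentrality d√(n/2) = 2.828d, exceeds ±2.042.

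| True d | Power |
|---|---|
| 0.3 | 0.13 |
| 0.5 | 0.28 |
| 0.8 | 0.59 |
| 1.0 | 0.78 |
| 1.02 | 0.80 |

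- 95% CI half-width: 2.042 × √(2/16) = 0.72 SD. An observed difference must therefore reach about 0.72 SD to be significant.
- If dropout left 14 or 13 per arm (assumed), the 80% figure would be 1.10 or 1.15 SD.
- Covariate adjustment multiplies the detectable difference by √(1 − r²), where r is the assumed correlation between baseline and the analysed score. With r = 0.5: 1.024 × 0.866 = 0.89 SD. With r = 0.7: 1.024 × 0.714 = 0.73 SD.

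**2. Inflation among significant results.** In 200,000 simulated trials with a true difference of 0.5 SD, the estimates significant in favour of rTMS averaged 0.91 SD.

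**3. Pre-post change in the rTMS arm (stated primary), n = 16.** The noncentrality is d√16 = 4d on 15 df, with critical value 2.131. Power is 0.46 at 0.5 SD and 0.85 at 0.8 SD, and reaches 0.80 at 0.75 SD. The half-width is 2.131/4 = 0.53 SD. These figures are better than in step 1, but no sample size makes an uncontrolled change attributable to rTMS.

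**4. Value for planning.** A pooled SD on 30 df has chi-square 95% limits of 0.80 to 1.34 times its estimate, so the variance limits are 0.64 to 1.79 times. The trial can supply this quantity, with that uncertainty, to a later sample-size calculation.

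**5. Texts side by side.** The synopsis, 6.A and 7.A ask for demonstration and significance. Section 1, 7.D and 13.2 (first paragraph) declare exploration. The second paragraph of 13.2 plans an efficacy model. None of these places says what a significant result from that model would mean.

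**The case against.** The best defence is that the exploratory purpose is already plain. The title carries the word, 7.D says confirmation belongs to later trials, and 13.2 repeats that the study is exploratory. This stands as mitigation. A size taken from earlier head-counts is then a declared choice, and the lack of a power calculation is not an error in such a trial.

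Two stronger readings are tempting, and the protocol supports neither. A reader might infer from the first paragraph of 13.2 that efficacy testing has been abandoned. That paragraph describes only the initial step, and the next one commits to a mixed model for efficacy. A reader might also infer that the trial cannot possibly meet its aim. A true difference near 1 SD would be detected with about 80% power, and a smaller one would suffice if covariates explain much of the variance, as the planned model allows.

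It is also fair to object that the rTMS-sham figures do not describe the primary named in the synopsis and 6.A, whose detectable effect is smaller. That is why both are given above.

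What the defence does not remove is the conflict in the objective and hypotheses themselves, or the silence on how a significant model result is to be read.

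**Conclusion.** The point holds as an inconsistency in the stated purpose that affects what the trial may conclude. The number of patients is not at fault. Sixteen per arm suits exploration. It supports a claim of demonstrated improvement over sham only if the effect is large: about 1.02 SD unadjusted, or roughly 0.7 to 0.9 SD under the assumed baseline correlations. A null result would leave an interval of ±0.72 SD around the estimate. The pre-post primary needs about 0.75 SD for 80% power but cannot separate rTMS from other causes of change.

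All these sizes rest on an assumed two-sided 5% level and t-test, because the protocol fixes neither, and on full follow-up except where stated. The inconsistency does not depend on them.

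**What to change.** 1. **Synopsis (Objectives) and 6.A:** state the aim as estimating the rTMS-sham difference in ADAS-Cog change at week 8 with its 95% CI, and the SD of that change, to plan a confirmatory trial.
2. **Synopsis (Primary outcome), 6.A (primary objective), 9.A and 13.1.A:** make that between-group difference the single primary outcome, and say in 13.1.A that the difference is between rTMS and sham. The pre-post change in the rTMS arm becomes descriptive or secondary. If only the aim were changed, it would conflict with the primary outcome.
3. **7.A:** replace the significance hypotheses with the estimation question.
4. **13.2:** reconcile the two paragraphs. Say that the mixed model's group-by-time estimate at week 8 is reported with its 95% CI as exploratory, and that no claim of demonstrated efficacy will be made from it.

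How a later trial allows for the uncertainty in the SD is for that trial to decide and need not be fixed here.

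**Cost:** wording only, with no added patients, visits or tests. The sponsor gives up an efficacy claim that the design does not support, and the pre-post change loses its primary status.
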